**Fig. 1 Fig1:**
[figure not shown]
Local Experienced Discomfort (LED) Questionnaire visual analogue scale

**Fig. 2 Fig2:**
[figure not shown]
Subjective Mental Effort Questionnaire (SMEQ) visual analogue scale

**Table 1 Tab1:** Study outline

Schedule	Enrollment	Surgery	Inpatient assessment	1st Outpatient follow-up	2nd Outpatient follow-up^c^
Assessment No.	1	2	3	4	5
Time	–6 weeks to 0	0	up to 1 week^b^	1mo^b^	1 year
Informed consent	x				
Medical history	x				
In-/exclusion criteria	x				
Physical examination	x		x	x	(x) ^c^
Registration	x				
Imaging^a^	x				
Randomization	x				
Questionnaire 1: LED (surgeon)		x			
Questionnaire :2 SMEQ (surgeon)		x			
Duration of surgery		x			
Intraoperative blood loss		x			
Intraoperative conversion		x			
Evaluation of complications			x	x	x
Length of hospital stay			x		
Costs of procedure			x		
Questionnaire 3: HR-QoL (patient)	x			x	x
Questionnaire 4: Cosmesis (patient)				x	x

Each x signifies one test, report, or procedure

^a^USS and/or CT and/or MRI abdomen

^b^In case of AE, inpatient assessment and/or outpatient FU-visit might exceed the given time limit; All patients will be assessed until the day of discharge and 3–4 weeks after surgery

^c^The 2nd postoperative follow-up of the patient may either be done in the outpatient clinic or the assessement may be conducted by phone. In case the patient is seen in the outpatient clinic, the insurance company of the participant will not be charged by the hospital

**Fig. 3 Fig3:**
[figure not shown]
Study flowchart

### Inclusion criteria

Patients fulfilling the following inclusion criteria may be enrolled in the study:Patient compliance and geographic proximity allow proper preoperative check-up and postoperative follow-upWritten informed consent given by the patientWomen who are not breastfeeding and are not pregnantAge ≥18 yearsSymptomatic cholecystolithiasisChronic cholecystitisBenign gallbladder polyps

### Exclusion criteria

The presence of one of the following criteria will lead to the exclusion of the subject:Significant systemic disease making the patient unsuitable for abdominal surgery (ASA IV and ASA V patients)Peritoneal carcinomatosis or other extensive metastatic diseaseMental or organic disorders which could interfere with giving informed consent or receiving treatmentsContraindications to pneumoperitoneumSuspicion of malignant diseasePrevious extensive upper abdominal surgery (upper gastrointestinal, hepato-pancreatico-biliary, colon, vascular and retroperitoneal surgery via laparotomy in the upper abdomen)Acute cholecystitisEmergency cholecystectomyObesity II°-III° (BMI > 35.0 kg/m2)

All patients that have been excluded from participation will be recorded together with the reason for the exclusion.

### Randomization and blinding

Non-stratified block randomization (random block sizes two and four) will be used to achieve balance in the allocation of participants to both treatment arms and prevent a premature decoding of the randomization scheme. Hereby, the patient will not be informed about the group assignment until the last outpatient follow-up and only after he/she has completed and returned all required questionnaires (GIQLI and BIQ).

### Participating surgeons and clinic

The operation will be performed according to the group assignment by three senior surgeons only, who have extensive experience in both robotic Single-Site and conventional single-incision laparoscopy. All participating surgeons received a one-day training in both approaches (robotic Single Site and laparoscopic single incision cholecystectomy). All surgeries will be performed at the Department of Surgery at the Cantonal Hospital of Winterthur (Kantonsspital Winterthur) in Switzerland.

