### Endpoints and data collection

The primary endpoint of the study is the surgeon’s physical and mental stress load at the time of surgery and is assessed by two validated visual analogue scales, specifically a modified Local Experienced Discomfort (LED, Fig. 1) and Subjective Mental Effort Questionnaire (SMEQ, Fig. 2) [7, 15]. Secondary endpoints include intra-operative blood loss, operating time, intra-operative conversion rate and additional trocar placement, complications, length of hospital stay, costs of procedure, Health-Related Quality of Life (HRQoL) and cosmesis. HRQoL and cosmesis will be assessed using the validated Gastrointestinal Quality of Life Index (GIQLI) and the Body Image Questionnaires (BIQ), respectively [16, 17]. The exact type and time of data collection is listed in detail in Table 1, the study flowchart is depicted in Fig. 3. All data will be recorded safely using the SecuTrial™ program. The estimated total duration of the study is 1.5 years, including the scheduled 1-month and 1-year postoperative follow-up visits. At the time of writing, the study is still active and the recruitment of patients has just been completed.

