### Power of the study

Sample-size calculations are based on the results of the previously mentioned experimental setup by Schatte et al. [7], utilizing an estimated effect size of 0.8, at a power of 0.8 and an alpha-error level of 0.05, as well as considering a potential additional error margin of 10–15% of the calculations (G-Power 3.1 software, Heinrich-Heine University Duesseldorf/Germany). The sample-size calculations resulted in a number of 30 randomized patients per arm (60 patients in total).

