### Statistical analysis

For descriptive statistics, median and mean with standard deviation will be used. For inductive statistics, the Chi-square and Fisher’s Test will be used to analyse contingency tables. In normally distributed data, a parametric two-sided Student’s T-Test (unpaired) to compare the data distributions in the two groups. In data that deviate from normal distribution, a two-tailed Mann–Whitney test will be applied to compare the data distributions in the two groups. All statistical analyses will be performed using SPSS (Version 22.0 and subsequent versions). P-values below 0.05 will be considered significant. No interim analyses are planned for the study.

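### The primary stress ratings all come from three surgeons, but the stated unpaired tests ignore surgeon; adjusting for surgeon would recover precision and protect against an uneven surgeon mix

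*Protocol article*

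**What the plan says.** Under Endpoints and data collection, the protocol article states: "The primary endpoint of the study is the surgeon’s physical and mental stress load at the time of surgery". It is measured by LED and SMEQ, and Table 1 marks both questionnaires as completed by the surgeon at the time of surgery.

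Under Participating surgeons and clinic: "The operation will be performed according to the group assignment by three senior surgeons only". The same section describes all three as experienced and trained in both techniques.

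Under Randomization and blinding: "Non-stratified block randomization (random block sizes two and four) will be used to achieve balance".

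Under Statistical analysis, normally distributed data get "a parametric two-sided Student’s T-Test (unpaired) to compare the data distributions in the two groups"; otherwise "a two-tailed Mann–Whitney test will be applied to compare the data distributions in the two groups". Neither test contains a surgeon term.

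Under Power of the study, the sample size rests on "utilizing an estimated effect size of 0.8, at a power of 0.8 and an alpha-error level of 0.05", plus a margin of 10–15%, giving 30 per arm. Endpoints and data collection adds that recruitment has just been completed.

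**The concern.** A self-rated stress score depends on who does the rating. People use a visual analogue scale differently, and three surgeons will supply all the values. An unpaired test treats the 60 ratings as exchangeable within each arm and leaves any difference between surgeons in the error term. That costs power on the primary endpoint.

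The same omission leaves the comparison unprotected if the three surgeons' shares of cases differ between arms. Part of any difference between techniques would then be a difference between raters. The article says that the operation follows the allocation, but not how or when the operating surgeon is chosen. An article may reasonably leave that scheduling detail out. It does mean that a reader cannot tell from the text whether surgeon is independent of arm.

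**Working it through.** **Inputs.** From the article: three surgeons; 30 per arm; effect size d = 0.8; two-sided alpha 0.05; power 0.8; unpaired test. Assumed, because the article gives no value: the share ρ of total rating variance that lies between surgeons (10%, 30%, 50%); equal surgeon shares unless stated; d expressed in total SD units, with total variance 1.

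**1. The plan's own figure.** A two-sided two-sample t-test (noncentral t) with d = 0.8 needs 26 per arm, at power 0.807. Adding the margin: 26 × 1.10 = 28.6, so 29; 26 × 1.15 = 29.9, so 30; 26 / 0.85 = 30.6, so 31. The stated 30 per arm reproduces, as a calculation for two groups of independent values.

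**2. Power at 30 per arm, surgeon independent of arm.**
- Unadjusted: noncentrality 0.8 × √(30/2) = 3.10 on 58 df gives power 0.861, whatever ρ is.
- Adjusted for surgeon: the residual SD is √(1 − ρ), so the effective effect is 0.8/√(1 − ρ), on 60 − 4 = 56 df.

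| ρ | Effective d | Noncentrality | Power, adjusted (formula) | Power, adjusted (simulated) |
|---|---|---|---|---|
| 10% | 0.843 | 3.27 | 0.894 | 0.88 |
| 30% | 0.956 | 3.70 | 0.953 | 0.95 |
| 50% | 1.131 | 4.38 | 0.990 | 0.99 |

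The formula takes surgeons as balanced across arms. The simulation (10,000 runs per setting) lets their counts vary at random, hence the slightly lower first value. With ρ = 0, simulated power is 0.861 unadjusted and 0.849 adjusted, so needless adjustment costs about one point.

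**3. Type I error in the same setting.** Simulated rejection under no effect is about 5% for both the unadjusted and the adjusted analysis at every ρ.

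**4. Chance imbalance.** With equal shares, a given surgeon's count in each arm is binomial (30, 1/3). The exact probability that the two counts differ by 6 or more is 0.13.

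**5. If surgeon mix depended on arm (hypothetical).** Take three equally spaced surgeon effects −a, 0, +a. With equal shares their variance is 2a²/3 = ρ, so a = √(1.5ρ); at ρ = 30%, a = 0.671. If the two extreme raters swap shares between arms, the bias is 2a times the difference in share.
- Mix 43/33/24% versus 24/33/43%: 2 × 0.671 × 0.19 = 0.25 SD; simulated type I error 16%.
- Mix 50/30/20% versus 20/30/50%: 2 × 0.671 × 0.30 = 0.40 SD; simulated type I error about 34%.

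These figures put the highest and lowest raters exactly where the shares swap. With raters placed at random among the same shares, the rates are about 11% and 20%. The surgeon-adjusted model stays near 5% throughout.

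**The case against.** The strongest defence is that surgeon is crossed with arm: all three surgeons work in both techniques, and nothing says that any of them took more cases of one. Operating according to the assignment most naturally means doing the allocated operation, not choosing the operator by arm. On that reading the planned test is valid, chance imbalance is already covered by its 5% error rate, and 86% power exceeds the 80% target. All of this stands.

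A reader might go further and infer that three raters make the unpaired test invalid, or that the trial's false-positive rate is 16% or 34%. The article does not support that. Those rates need an arm-dependent surgeon mix that it does not describe, together with a worst-case alignment of raters and shares. Nor does the usual cluster design effect apply, since surgeons are not nested within arms.

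It can also be said that covariate adjustment belongs in an analysis plan that is not shown. That stands in part: such a plan may contain it. But the article does not leave the comparison open. It fixes non-stratified allocation and names unpaired tests, so the point concerns a stated choice and not a missing detail.

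**Conclusion.** The point holds as a loss of precision on the primary endpoint, with a conditional risk of bias. With surgeon independent of arm, the stated test is sound but less powerful than it could be: about 86% against roughly 89%, 95% and 99% at assumed between-surgeon shares of 10%, 30% and 50%. The size of the gain rests wholly on that share, for which the article gives no value.

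Bias follows only if the choice of surgeon depended on arm. Under the skewed mixes assumed above and a 30% share, type I error would then be roughly 10–35%, depending on the mix and on which surgeons rate high or low. This shows what adjustment guards against; it is not an estimate of what happened in this trial.

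With three surgeons, the result describes these three whatever the analysis, which is narrower than the Discussion's hope of guiding surgeons in general. The change should be made because it is cheap, not because the planned test is wrong.

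**What to change.** Before the data are analysed, specify the primary comparison of each scale as a linear model with arm and surgeon as fixed effects, or a van Elteren test stratified by surgeon where ranks are needed, in place of the unpaired test. Report the number of cases per surgeon per arm and each surgeon's own arm difference, and say how the operating surgeon was chosen. Limit the conclusion to these three surgeons. With recruitment complete, stratifying the randomisation is no longer possible, so this is an analysis change only.

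The cost is two degrees of freedom and about 1–2 points of power if surgeons do not differ; no extra patients are needed. The operating surgeon must be retrievable for every case. Table 1 has no item for it, so this should be confirmed first.

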### Power of the study

Sample-size calculations are based on the results of the previously mentioned experimental setup by Schatte et al. [7], utilizing an estimated effect size of 0.8, at a power of 0.8 and an alpha-error level of 0.05, as well as considering a potential additional error margin of 10–15% of the calculations (G-Power 3.1 software, Heinrich-Heine University Duesseldorf/Germany). The sample-size calculations resulted in a number of 30 randomized patients per arm (60 patients in total).

### Statistical analysis

For descriptive statistics, median and mean with standard deviation will be used. For inductive statistics, the Chi-square and Fisher’s Test will be used to analyse contingency tables. In normally distributed data, a parametric two-sided Student’s T-Test (unpaired) to compare the data distributions in the two groups. In data that deviate from normal distribution, a two-tailed Mann–Whitney test will be applied to compare the data distributions in the two groups. All statistical analyses will be performed using SPSS (Version 22.0 and subsequent versions). P-values below 0.05 will be considered significant. No interim analyses are planned for the study.

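### The enrolment GIQLI score is collected, but the tests named for continuous data do not adjust for it, so the quality-of-life comparison gives up precision at no saving

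*Protocol article*

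**What the plan says.** Endpoints and data collection lists quality of life among the secondary endpoints, measured with the "validated Gastrointestinal Quality of Life Index (GIQLI"). In Table 1 the row beginning "Questionnaire 3: HR-QoL (patient" is marked at enrolment (up to 6 weeks before surgery), at 1 month and at 1 year, so a preoperative score is scheduled for every patient.

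Statistical analysis is one paragraph covering all endpoints. For continuous data it names two procedures. If the data are normal, it is "a parametric two-sided Student’s T-Test (unpaired) to compare the data distributions in the two groups". If not, "a two-tailed Mann–Whitney test will be applied to compare the data distributions in the two groups". No covariate, change score, repeated-measures model or other use of the enrolment score is mentioned.

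Randomization and blinding describes block randomisation without stratification. Power of the study says that the calculations "resulted in a number of 30 randomized patients per arm (60 patients in total").

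**The concern.** Two independent-sample tests are the only inferential methods given for an outcome that has its own baseline. Part of the between-patient spread in GIQLI after surgery is usually predictable from the score before surgery. A two-group test on follow-up scores leaves that part in the error term. With 30 per arm and nothing in the design to balance enrolment GIQLI, the arms may also differ at the start by chance, and some of that difference carries through to follow-up.

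Study objectives says that the robotic approach should lower surgeon stress while keeping up with the conventional approach on peri- and postoperative outcomes. GIQLI is one of two patient-reported measures bearing on the second half of that statement. A claim that outcomes match needs a narrow interval, because a non-significant p-value from an imprecise comparison says little. The article reports that recruitment has just finished, so precision can no longer be bought with more patients.

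**Working it through.** **Inputs from the article.** 30 per arm; two-sided alpha 0.05; power 0.8; standardised effect 0.8 (set for the primary endpoint, not for GIQLI); margin 10–15%; GIQLI at three time points.

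**Assumed.** The correlation rho between enrolment and follow-up GIQLI is not given, so 0.3, 0.5 and 0.6 are used. Equal SDs at both times and no missing scores are also assumed.

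**1. The plan's own figure.** Under the normal approximation, n = 2(1.96 + 0.84)²/0.8² gives 25 per arm. The exact two-sided t-test gives 26. Inflating by n/(1 − d) gives 26/0.90 = 28.9, so 29, and 26/0.85 = 30.6, so 31. Inflating by n(1 + d) gives 29 and 30. The stated 30 is reproduced and is not in dispute.

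**2. Precision.** In units of the variance of the unadjusted follow-up comparison, ANCOVA has factor 1 − rho² and a change-score comparison has factor 2(1 − rho). Their ratio, ANCOVA to change score, is (1 + rho)/2. The unadjusted t-test would need 30/(1 − rho²) per arm to match ANCOVA. Detectable difference and power come from the noncentral t with 30 per arm (58 df unadjusted, 57 df ANCOVA).

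| Analysis | Variance factor | Matching n per arm | Detectable at 80% power | Power for 0.5 SD | Change-score factor | ANCOVA / change score |
|---|---|---|---|---|---|---|
| Unadjusted | 1.00 | 30 | 0.74 SD | 48% | – | – |
| ANCOVA, rho 0.3 | 0.91 | 33 | 0.70 SD | 51% | 1.40 | 0.65 |
| ANCOVA, rho 0.5 | 0.75 | 40 | 0.64 SD | 59% | 1.00 | 0.75 |
| ANCOVA, rho 0.6 | 0.64 | 47 | 0.59 SD | 66% | 0.80 | 0.80 |

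The matching sample sizes correspond to 10%, 33% and 56% more patients. Estimating the slope with 60 patients costs about 2% of variance, which the table leaves out. With it, the factors become about 0.91 × 1.02 = 0.93, 0.75 × 1.02 = 0.77 and 0.64 × 1.02 = 0.65.

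Because (1 + rho)/2 is below 1 for every rho below 1, ANCOVA also beats a change-score test. Below rho 0.5, a change score is worse than leaving the baseline out.

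**3. Chance imbalance.** The standard error of the baseline mean difference is SD × √(2/30) = 0.26 SD. An imbalance above 0.25 SD in either direction has probability about 33%, and one above 0.5 SD about 5%.

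- If follow-up scores are tested, the shift in the result is rho times the imbalance. For 0.3 SD this is 0.3 × 0.3 = 0.09 SD up to 0.6 × 0.3 = 0.18 SD.
- If change scores are tested, it is −(1 − rho) times the imbalance. For 0.3 SD this is −0.7 × 0.3 = −0.21 SD to −0.4 × 0.3 = −0.12 SD.
- For the unadjusted follow-up test, type I error given a 0.5 SD imbalance is about 8% at rho 0.3 and 13% at rho 0.5. Given 0.25 SD it is 4.9% and 4.7%, close to nominal. Averaged over all randomisations it is 5%.

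**The case against.** The strongest reply is that nothing here is an error. Under randomisation the unpaired test is unbiased, and its standard error already includes the variation due to chance baseline differences. A reader might infer that the planned analysis is biased or has an inflated error rate. The documents do not support that: the excess arises only conditionally, given a sizeable imbalance in the arms actually drawn, and it is attenuated by rho if follow-up scores are tested.

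A reader might also infer that the plan tests raw follow-up scores separately at each visit and ignores the baseline. The Statistical analysis section does not say so. It names neither GIQLI, nor a visit, nor the quantity compared, and a t-test on change from enrolment would fit the same words. This part of the objection stands, so the point is put as a lack of adjustment. It does not rescue the plan, since a change-score test is also less efficient than ANCOVA.

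A third reply is that covariates for one secondary questionnaire belong in a fuller document that is not shown. That has some force, and such a document may already adjust. But the article does not leave the method open: it names the tests, and they are poorly suited to an outcome with a scheduled baseline.

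Lastly, the benefit depends on a correlation that the documents do not give. The two scores may be more than a year apart with an operation in between, so a low value cannot be excluded. This stands too.

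**Conclusion.** The point holds as an efficiency weakness in the analysis of one secondary endpoint. The tests named for continuous data do not adjust for the enrolment GIQLI, although that score is scheduled for every patient. They remain valid.

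The size rests on the assumed rho. At 0.3 the gain is small: 9% of variance before the slope cost, and a detectable difference of 0.70 instead of 0.74 SD. At 0.5 to 0.6 it is worth having, at 25% to 36% of variance. Even then the trial is not well powered for a 0.5 SD difference in GIQLI (59% to 66%), so adjustment improves the comparison without making it conclusive.

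The primary endpoint (LED and SMEQ, recorded only at surgery), BIQ (recorded only at 1 month and 1 year) and the sample size are unaffected.

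**What to change.** State before the GIQLI arms are compared:

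- GIQLI at 1 month and at 1 year is analysed by ANCOVA with arm and enrolment GIQLI as terms. Alternatively, one mixed model covers both visits, with arm, visit, arm-by-visit and enrolment GIQLI.
- The result is reported as the adjusted mean difference with its 95% CI.
- If residuals are clearly non-normal, a rank-based or bootstrap version of the adjusted analysis is used.
- The unadjusted t-test or Mann–Whitney test is kept as a supporting analysis, with a statement of whether it uses follow-up or change scores.

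If a separate analysis plan already adjusts for enrolment GIQLI, it is enough to say that it replaces the general wording for this endpoint. The cost is a few lines of text. No further data, visits or patients are needed, and SPSS, the software already named, fits ANCOVA and mixed models. Table 1 places both the questionnaire and randomisation at enrolment; since patients are blinded to their arm, the enrolment score is usable as a covariate.

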### Ethics

The study will be carried out in accordance with principles enunciated in the current version of the Declaration of Helsinki, the guidelines of Good Clinical Practice (GCP) issued by ICH, and Swiss regulatory authority’s requirements. The principal investigator has completed a GCP course (modules 1–3). The study has been approved by the local ethics committee (Kantonale Ethikkommission Zürich, KEK-ZH-Nr. 2014–0114) and was registered at clinicaltrials.gov (trial number: NCT02485392).

### Surgical technique

The Single Site robot-assisted cholecystectomy using the da Vinci Si platform is performed according to the manufacturer´s instructions (Intuitive Surgical, Sunnyvale, CA, USA). The patient is placed in supine position under general anaesthesia, followed by surgical disinfection and sterile draping. A 2.0–2.5 cm midline intra-umbilical incision down to the level of the fascia is created using standard surgical technique. The fascia is incised and the abdomen is entered under direct vision. Subsequently, the fascial incision is enlarged to 2.5 cm and a finger sweep to check for adhesions is performed. Next, the surgeon inserts the Single-Site port using an atraumatic clamp. The Single-Site Port has a target anatomy arrow indicator and five lumens: four to hold cannulae (one 8.5 mm da Vinci Endoscope Port, two 5 mm Single-Site Instrument Arm Ports and one 5 mm Accessory Port) and one lumen for the insufflation adapter. After proper alignment of the Port, the table is placed in reverse Trendelenburg anatomy (~10–15°) under visual guidance (30° down endoscope) and docking is performed, whereby the patient cart approaches the patient from the right side in a ~45° angle. In contrast to the single incision conventional laparoscopic approach, the robotic technique utilizes ergonomic, curved robot-assisted laparoscopic devices that preserve triangulation within the operative field. The control of the crossing instruments is independently reassigned to the opposite side by the robotic software. The available accessories include curved scissors, hook, clip applier, needle driver, Cadiere grasper, Maryland retractor and also a suction-irrigation device. In addition, a laparoscopic grasper is inserted through the accessory cannula, which is utilized to retract the gallbladder fundus up and toward the patient’s right shoulder by the first assistant who is positioned on the left of the patient. After completion of the docking procedure, the console surgeon first dissects the Calot’s Triangle in a standard fashion, subsequently ligates and divides the cystic duct and artery, performs a gallbladder bed dissection and extracts the gallbladder specimen using a 10 mm EndoPouch Retriever™ instrument which is inserted through the accessory port after removal of the 5 mm assistant cannula. All instruments and the cannula are removed under visual guidance, the da Vinci Si platform is undocked and the Single Site port is removed together with the gallbladder and the specimen bag through the single incision. Lastly, the fascial defect is closed with 0 Vicryl and a subcuticular skin closure with 4/0 or 5/0 Monocryl is performed.

The single-incision laparoscopic cholecystectomy is performed as previously described with slight modifications [5]. In brief, a 2.0–2.5 cm midline intra-umbilical skin and fascia incision is performed and a SILS™ PT12 Port (Covidien Inc., Norwalk, California, USA) is introduced. This port obtains four openings: one for gas insufflation and three that can accommodate trocars ranging from sizes 5 – 12 mm. A 5-mm 45° long scope (HD EndoEye™, Olympus Europa Holding GmbH, Hamburg, Germany) is introduced through one of the openings in the SILS™ Port. The patient is then placed in an anti-Trendelenburg position. The fundus of the gallbladder is grasped and the EndoGrab™ (Virtual Ports Ltd., Caesarea, Israel) internally anchored retraction system is introduced (Endograsp roticulator™, Covidien Inc., Norwalk, California, USA). As an alternative, the TriPort Plus™ multitrocar port can be utilized (Olympus, Tokyo, Japan). The dissection of the Calot’s Triangle is done using a monopolar dissection hook. The cystic artery and duct are first dissected and then separately clipped with a standard 5 mm clip applicator (Covidien, Norwalk, California, USA). The gallbladder bed dissection is performed and once the gallbladder is free from the adjacent tissues, the 5 mm trocar is exchanged for a 10 mm trocar. An Endocatch bag (Endocatch Gold, 10 mm; Covidien Inc., Norwalk, California, USA) is inserted and the gallbladder is extracted. The umbilical fascia is closed using absorbable 0 Vicryl suture and a subcuticular skin closure with 4/0 or 5/0 Monocryl is performed.

